## 4.3. Withdrawal Criteria

Subjects will be withdrawn from study treatment for any of the following:

1. Inability to fully comply with the study protocol

2. Unacceptable toxicity

3. Patients refused to continue the study at any time after the randomization

4. Best interest of the subject based upon the investigator’s discretion

# 5. Study Procedures

## 5.1 Treatment Assignment

Patients who meet the eligibility criteria and consent to participate will be randomized at 1:1 ratio to receive 7.5 mg/kg ATG (7.5 mg group, experimental Group) or 10.0 mg/kg ATG (10.0 mg group, control group).

## 5.2 Study Treatment

ATG (Thymoglobulin; rabbit anti-human thymocyte immunoglobulin, Imtix Sangstat, Lyon, France) will be administered in 2.5mg/kg/day from days -3 to -1 in 7.5 mg group, and days -4 to -1 in 10.0 mg group. If ATG-related diarrhea or grade III fever (according to the Common Terminology Criteria for Adverse Events, the CTCAE, version3.0) occurred, additional dexamethasone (5.0 mg) would be given for treatment, and the speed of ATG infusion would be slowed down. If the subject experienced severe ATG associated allergic reaction at the first dose, he will be excluded from the study.

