## 4.2. Removal Criteria

Subjects who have participated in the study will be removed from statistical analysis for any of the following:

1. Subjects who are ineligible for this study

2. Deviation(s) from the protocol

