# 6. Efficacy Assessments

## 6.1 Definition

1. Hematopoietic engraftment was defined as the first of 3 consecutive days with an absolute neutrophil count exceeding 0.5×10^9^/L, and platelet reconstitution was defined the first day of a platelet count >20×10^9^/L without platelet transfusion Primary poor graft function (PGF) is defined as a slow or incomplete recovery of blood cell counts (ANC ≤0.5×10^9^/L and PLT ≤20×10^9^/L) by days +30 post-transplantation.

2. CMV viremia means positive CMV-DNA in the blood twice consecutively.

3. EBV viremia means positive EBV-DNA in the blood twice consecutively.

4. EBV-associated diseases are classified into EBV-associated post-transplant lymphoproliferative diseases (PTLD) and EBV-associated other diseases. The diagnosis of EBV-associated PTLD is according to the criteria of World Health Organization (WHO). The diagnosis of EBV-associated other diseases is based on the criteria of the European Conference on Infections in Leukemia and literatures, which include EBV-associated diseases with tissue other than lymphatic tissue involvement [see appendix 1].

5. The diagnosis of CMV-associated disease is according to the criteria of the European Conference on Infections in Leukemia [see appendix 2].

6. aGVHD is defined according to the 1994 Consensus Conference on Acute GVHD Grading and graded from I to IV grades, and cGVHD is graded as limited and extensive according to the literature [see appendix 3].

7. Relapse is defined as as hematologic relapse that were re-appearance of blasts in the peripheral blood, any manifestation of leukemia outside the hematopoietic system, or >5% blasts in the BM smear.

8. NRM is defined as death without relapse.

9. OS refers to survived until the final follow-up time point.

10. DFS is defined as survival in continuous CR without relapse.

11. Tolerability is evaluated based upon clinical symptoms and laboratory abnormalities (adverse events of ATG assessed according to the CACTE, version3.0). The clinical symptoms include the symptoms may be associated with the administration of ATG reported previously, including headache, arthralgia, bone pain, fatigue, fever, lightheadedness, petechiae, mucositis and diarrhea. The index of adverse events include hepatic function (ALT, AST, TBIL, DBIL) and renal function (BUN, Scr).

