## 6.4 Methods and Schedule Of endpoints assessments

Patients will be followed for adverse events for 30 days after study treatment post-transplantation. The CMV-DNA and EBV-DNA loads of blood will be detected regularly by quantitative real-time polymerase chain reaction (RQ-PCR). The threshold for EBV-DNA and CMV-DNA copies in plasma provided by the manufacturer (ZJ Bio-Tech Co., Ltd., Shanghai, China) is less than 500 copies/ml. EBV-DNA or CMV-DNA is considered positive when the copies exceeded 500 copies/ml. The CMV-DNA and EBV-DNA of blood is monitored weekly for the first 3 months after transplantation; during the 4^th^ to 9^th^ month post-transplantation, the monitoring frequency was once every 2 weeks; and the frequency was once a month for the 10^th^ to 12^th^ month. If positive, viral load will be monitored twice a week. Endpoints assessments will be assessed according to the criteria previously mentioned throughout the study period.

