## 7.2 Adverse Events

The investigator is required to make an assessment of the toxicity grade of each adverse events (AE) or serious adverse events (SAE) reported. In this protocol, the toxicity grade of each AE/SAE will be evaluated according to the CTCAE version 3.0.

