# 8. Rules of Follow-Up

## 8.1 Follow-up Period

Starting after completion of ATG treatment or withdrawal from the study for other reasons.

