### 9.2.2 Analysis of safety

All the patients in the study will be included in the safety analysis. The safety end points included clinical symptoms and laboratory abnormalities, laboratory values and vital signs analyzed by means of the chi-square test.

All P values are based on two-sided hypothesis tests. Alpha is set at 0.05. SPSS 19.0 (SPSS Inc., Chicago, IL, USA) and R version 3.4.3 (R Development Core Team, Vienna, Austria) were used for all data analysis.

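### Patients with a severe allergic reaction to the first ATG dose are excluded from the study after randomisation, and nothing keeps them in the safety or efficacy analysis

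*Protocol*

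**What the plan says.** Patients are randomised once they are found eligible and have consented (section 5.1), and ATG follows. Section 5.2 then provides: "If the subject experienced severe ATG associated allergic reaction at the first dose, he will be excluded from the study". Section 4.3 lists unacceptable toxicity as a reason for withdrawal, but from study treatment, not from the study.

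For the analysis, section 9.2.2 states: "All the patients in the study will be included in the safety analysis". Section 4.2 adds a further route out of the analysis, for ineligibility or protocol deviations: "Subjects who have participated in the study will be removed from statistical analysis for any of the following".

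On timing, section 6.4 states: "Patients will be followed for adverse events for 30 days after study treatment post-transplantation". Section 8.1 describes follow-up as "Starting after completion of ATG treatment or withdrawal from the study for other reasons". Neither names the first infusion as the start of adverse event collection. Section 7.2 requires grading of whatever is reported: "The investigator is required to make an assessment of the toxicity grade of each adverse events (AE) or serious adverse events (SAE) reported".

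Tolerability is a listed secondary endpoint (section 6.3). Section 6.1 defines it by symptoms linked to ATG, "including headache, arthralgia, bone pain, fatigue, fever, lightheadedness, petechiae, mucositis and diarrhea", together with liver and kidney laboratory values.

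**The concern.** The exclusion is triggered by an effect of the study drug in a patient already randomised and dosed. Section 4.3 ends treatment for toxicity in general, whereas section 5.2 ends study participation for one particular severe toxicity, and the protocol does not explain the difference. Since section 9.2.2 defines the safety analysis by being in the study, the plain reading leaves these patients out.

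Two things are at stake. The reported frequency of severe allergic reactions to ATG would omit those at the first dose. And randomised patients would be lost from the comparison of assigned arms because of something that happened after randomisation. If they also leave follow-up, no later analysis decision can restore their outcomes.

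**Working it through.** **The passages side by side**

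| Section | What it settles | What it leaves open |
| --- | --- | --- |
| 4.3 | Toxicity ends study treatment | – |
| 5.2 | A severe first-dose allergic reaction ends study participation | Whether follow-up continues |
| 8.1 | Follow-up starts after ATG completion, or after withdrawal for other reasons | Whether a 5.2 exclusion is such a withdrawal |
| 9.2.2 | Safety covers all patients in the study | Whether a 5.2 exclusion is still in the study |
| 6.4 | Adverse event follow-up lasts 30 days after treatment | The day on which collection starts |

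Sections 4.3 and 5.2 treat severe toxicity differently, and neither 8.1 nor 9.2.2 resolves the difference.

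**The plan's own sample size.** Inputs from section 9.1.1: 30% versus 42%, one-sided 5%, 80% power, 1:1 allocation, 5% drop-out. With unpooled variance:

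n = (1.645 + 0.842)² × (0.30×0.70 + 0.42×0.58) / 0.12² = 6.183 × 0.4536 / 0.0144 = 194.75, so 195 per group.

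195 / 0.95 = 205.3, so 206 per group and 412 in total. The stated figure is reproduced.

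**Patients affected.** The protocol gives no rate r of severe first-dose allergic reactions, so the range is an assumption.
- r = 1%: 412 × 0.01 = 4.1 patients
- r = 2%: 412 × 0.02 = 8.2 patients
- r = 3%: 412 × 0.03 = 12.4 patients

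The 5% drop-out allowance is 412 × 0.05 = 20.6 patients.

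**Effect on the reported rate.** Let q be the rate of severe reactions at later doses among those who continue, here assumed to be 1%. The true rate is r + (1 − r)q. If the 5.2 patients leave the safety set, the reported rate is q.

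| r | True rate | Reported rate |
| --- | --- | --- |
| 1% | 1.99% | 1% |
| 2% | 2.98% | 1% |
| 3% | 3.97% | 1% |

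The first-dose component is reported as zero, so it is understated by the whole of r.

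**Effect on power.** Chi-square approximation with pooled variance under the null, one-sided 5%, n = 206 × 0.95 × (1 − r) per arm:
- r = 0: n = 195.7, power 79.8%
- r = 1%: n = 193.7, power 79.5%
- r = 2%: n = 191.8, power 79.1%
- r = 3%: n = 189.8, power 78.7%

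These figures place the exclusions on top of the full 5% drop-out. If they fall within that allowance, the loss is smaller.

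**Effect on the contrast between arms.** Section 5.2 gives 2.5 mg/kg per day in both groups, so the first dose is identical. First-dose exclusions should therefore be roughly balanced. The additional infusion in the 10.0 mg/kg group cannot trigger a first-dose rule.

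**The case against.** The strongest reply is that section 9.2.2 is inclusive: it says that all patients are analysed and does not say that 5.2 exclusions are left out. The exact safety set is commonly defined in a statistical analysis plan, and section 9.2 refers to one. This stands in part, since a SAP could count every treated patient. But the exclusion is a protocol rule, and if it ends follow-up, a SAP cannot supply the missing outcomes.

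A second reply is that the numbers are small and balanced, and that section 4.1.3 already excludes patients with known anaphylaxis to ATG. This stands. It limits the point to absolute rates and to keeping patients as randomised.

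A reader might infer two stronger claims that the protocol does not support:

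- **That infusion days are outside adverse event collection.** Section 6.4 says how long follow-up lasts after treatment, not that collection begins then. Section 8 governs follow-up visits, and 8.1 also names withdrawal as a starting point. Section 5.2 expects graded events during infusion ("If ATG-related diarrhea or grade III fever (according to the Common Terminology Criteria for Adverse Events, the CTCAE, version3.0) occurred"), and 7.2 has every reported event graded without a start date. The start is unstated; it is not set after the infusions.
- **That severe ATG reactions in general would be reported near zero.** The rule reaches only severe allergic reactions at the first dose. Later-dose reactions and severe non-allergic ones, such as grade III fever, remain reportable. The symptoms listed for tolerability do not include allergic reaction, so the endpoint as listed is largely untouched.

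**Conclusion.** The point holds in a limited form. As written, section 5.2 removes randomised, treated patients from the study because of a severe reaction to the study drug. It does not fit section 4.3, and no section keeps these patients in the safety analysis or in the assigned-arm comparison.

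The size depends on an assumed first-dose rate of 1% to 3%, that is about 4 to 12 of 412 patients, and on reading 9.2.2 as leaving them out. On that basis the severe first-dose rate is understated in full, while the loss of power is about one percentage point or less. Material bias between arms is not expected, because the first dose is the same. The consequence is mainly for the absolute rate of severe reactions and for the principle of analysing patients as randomised. The EBV DNAemia result is little affected.

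**What to change.** Reconcile sections 4.3, 5.2, 8.1 and 9.2.2 so that the following is explicit:

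1. A patient with a severe first-dose allergic reaction remains in study follow-up and in the efficacy analysis of the assigned arm. Section 4.2 should not be applied so as to remove such a patient.
2. The safety set is every patient who receives any ATG.
3. Section 6.4 states that adverse event collection runs from the first ATG infusion to the end of the existing 30-day period. Sections 5.2 and 7.2 already imply this start.

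The cost is protocol and SAP wording, plus continued data collection for a handful of patients. No change in sample size is needed. The downside for the sponsor is that the reported severe-reaction rate may rise slightly. No position is taken on how ATG is managed after such a reaction.

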# 6. Efficacy Assessments

## 6.1 Definition

1. Hematopoietic engraftment was defined as the first of 3 consecutive days with an absolute neutrophil count exceeding 0.5×10^9^/L, and platelet reconstitution was defined the first day of a platelet count >20×10^9^/L without platelet transfusion Primary poor graft function (PGF) is defined as a slow or incomplete recovery of blood cell counts (ANC ≤0.5×10^9^/L and PLT ≤20×10^9^/L) by days +30 post-transplantation.

2. CMV viremia means positive CMV-DNA in the blood twice consecutively.

3. EBV viremia means positive EBV-DNA in the blood twice consecutively.

4. EBV-associated diseases are classified into EBV-associated post-transplant lymphoproliferative diseases (PTLD) and EBV-associated other diseases. The diagnosis of EBV-associated PTLD is according to the criteria of World Health Organization (WHO). The diagnosis of EBV-associated other diseases is based on the criteria of the European Conference on Infections in Leukemia and literatures, which include EBV-associated diseases with tissue other than lymphatic tissue involvement [see appendix 1].

5. The diagnosis of CMV-associated disease is according to the criteria of the European Conference on Infections in Leukemia [see appendix 2].

6. aGVHD is defined according to the 1994 Consensus Conference on Acute GVHD Grading and graded from I to IV grades, and cGVHD is graded as limited and extensive according to the literature [see appendix 3].

7. Relapse is defined as as hematologic relapse that were re-appearance of blasts in the peripheral blood, any manifestation of leukemia outside the hematopoietic system, or >5% blasts in the BM smear.

8. NRM is defined as death without relapse.

9. OS refers to survived until the final follow-up time point.

10. DFS is defined as survival in continuous CR without relapse.

11. Tolerability is evaluated based upon clinical symptoms and laboratory abnormalities (adverse events of ATG assessed according to the CACTE, version3.0). The clinical symptoms include the symptoms may be associated with the administration of ATG reported previously, including headache, arthralgia, bone pain, fatigue, fever, lightheadedness, petechiae, mucositis and diarrhea. The index of adverse events include hepatic function (ALT, AST, TBIL, DBIL) and renal function (BUN, Scr).

## 6.2. Primary Endpoint

Incidence of EBV DNAemia within 1 year post-transplantation

## 6.3 Secondary Endpoints

1. The incidences of grade II to IV and grade III to IV aGVHD within 100 days post-transplantation.

2. Hematopoietic engraftment

3. EBV-associated diseases

4. CMV infections (CMV DNAemia and associated diseases)

5. cGVHD

6. Relapse

7. NRM

8. OS

9. DFS

10. Tolerability

## 6.4 Methods and Schedule Of endpoints assessments

Patients will be followed for adverse events for 30 days after study treatment post-transplantation. The CMV-DNA and EBV-DNA loads of blood will be detected regularly by quantitative real-time polymerase chain reaction (RQ-PCR). The threshold for EBV-DNA and CMV-DNA copies in plasma provided by the manufacturer (ZJ Bio-Tech Co., Ltd., Shanghai, China) is less than 500 copies/ml. EBV-DNA or CMV-DNA is considered positive when the copies exceeded 500 copies/ml. The CMV-DNA and EBV-DNA of blood is monitored weekly for the first 3 months after transplantation; during the 4^th^ to 9^th^ month post-transplantation, the monitoring frequency was once every 2 weeks; and the frequency was once a month for the 10^th^ to 12^th^ month. If positive, viral load will be monitored twice a week. Endpoints assessments will be assessed according to the criteria previously mentioned throughout the study period.

# 7. Safety

## 7.1 Safety Endpoints

### 7.1.1 Clinical symptoms

The clinical symptoms include the symptoms may be associated with the administration of ATG reported previously.

 headache

 arthralgia

 bone pain

 fatigue

 fever

 lightheadedness

 petechiae

 mucositis

 diarrhea

### 7.1.2 Laboratory abnormalities: Incidence of adverse events, grade according to the CTCAE version3.0

 1. Hepatic function

 ALT

 AST

 TBIL

 DBIL

2. Renal function

 BUN

 Scr

## 7.2 Adverse Events

The investigator is required to make an assessment of the toxicity grade of each adverse events (AE) or serious adverse events (SAE) reported. In this protocol, the toxicity grade of each AE/SAE will be evaluated according to the CTCAE version 3.0.

# 8. Rules of Follow-Up

## 8.1 Follow-up Period

Starting after completion of ATG treatment or withdrawal from the study for other reasons.

## 8.2 Visit Scheduling

Every week for the first 3 months after transplantation, every two weeks during the 4th to 9th month post-transplantation, every month for the 10th to 24th month, and then every three months for the 25th to 36th month.

## 8.3 Contents

The contents of every follow-up visit include complaints of subjects, physical examination, hematology, urinalysis, biochemistry and viral loads in blood (EBV-DNA or CMV-DNA). All of the results must be documented in the original medical record.

# 9. Data Analysis and Statistical Considerations

## 9.1 Study Design Considerations

This is a prospective, multi-center, controlled, open-label, randomized (1:1) phase Ⅳ study of comparison of different dosages ATG for GVHD prophylaxis (7.5 mg/kg vs. 10.0 mg/kg) in patients receiving haplo-HSCT. The primary Endpoint was incidence of EBV DNAemia within 1 year post-transplantation, and the study is designed to determine if 7.5 mg/kg ATG is superior to 10.0 mg/kg in the study population with respect to EBV DNAemia.

### 9.1.1 Sample Size Assumptions

In the initial design, we predefined grade II to IV acute GVHD as the primary endpoint. We hypothesized that non-inferiority of 7.5 mg/kg ATG against 10.0 mg/kg ATG was established if the difference of the 95% CI in grade II to IV acute GVHD between the two groups was within 15%. On the assumption of an incidence of grade II to IV acute GVHD of 30%, an estimated 197 patients in each group were required at the one-sided significance level of 5% with a power of 90%. After the analysis of the first 210 patients enrolled in the study, the 100-day incidence of grade II to IV acute GVHD was 28.9% and 27.8% in the 7.5 mg/kg and 10.0 mg/kg groups with a difference of 1.2% with 95% CI of -10.0% to 13.4%. The 1-year incidence of EBV DNAemia in the 7.5 mg/kg group was significantly lower than that in the 10.0 mg/kg group (27.1% in 7.5 mg/kg group vs 45.2% in the 10.0 mg/kg group). According to the recommendation of the data and safety monitoring committee, the change of the primary endpoint was made to evaluate the superiority of a dose level of 7.5 mg ATG on viral infections without increasing aGVHD after haplo-HSCT.

The sample size calculation is with the following assumptions:

1. Incidence of EBV DNAemia within 1 year post-transplantation in 7.5 mg group: 30%
2. Incidence of EBV DNAemia within 1 year post-transplantation in 10.0 mg group: 42%
3. a 1:1 randomization scheme
4. a 5% 1-tailed risk of erroneously claiming a difference in the presence of no true underlying difference by Chi-square test or Fisher’s exact test
5. a 80% chance of successfully declaring a difference in the presence of a true underlying difference (power)
6. 5% percent of cases drop

Under the above assumptions, a total sample size of 412 subjects is required (206 in each group).

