# 1. Background

Allogeneic hematopoietic stem cell transplantation (allo-HSCT) has been regarded as a curative strategy for acute leukemia. Lack of HLA-matched donor is the obstacle to widespread application of allo-HSCT. A growing body of clinical studies has suggested that haplo-identical related donor HSCT (haplo-HSCT) has comparable outcomes with transplants from matched sibling and unrelated donor, following the improvement of transplant technique in the last few years, such as immunosuppressive conditioning, graft manipulation, infection and graft-versus-host disease (GVHD) management. As a result, haplo-identical related donor is now considered an alternative for allo-HSCT. However, GVHD and infections remain main causes of morbidity and mortality after haplo-HSCT except leukemia relapse.

Now, the strategies of GVHD prophylaxis mainly included ex vivo and in vivo T-cell-depletion (TCD) in haplo-HSCT. Although ex vivo TCD could reduce the morbidity and mortality of GVHD, it also affects immune reconstitution leading to high incidences of infections and disease relapse, and so on, making less benefit for survival. Therefore, ex vivo TCD has been gradually replaced by in vivo TCD. Among the in vivo TCD strategies, two major methods are used: antithymocyteglobulin (ATG)/antilymphocyte globulin (ALG) or post-transplantation cyclophosphamide (PTCy). The ATG strategy has been widely used, especially in China, resulting in a declined infections and relapse compared with ex vivo TCD. Nevertheless, infections, especially viral infections, remain important drawback of ATG strategy. Several studies have demonstrated the risk of infections depends on the dosage of ATG. To data, the optimal dose of ATG which offers sufficient efficacy of GVHD prophylaxis and minimizes risk of infections is unknown in the haplo-identical setting. In our previous single-center study, 6mg/kg rabbit-ATG had a lower incidence of EBV infection, but higher risk of severe acute GVHD (aGVHD) and chronic GVHD (cGVHD) in haplo-HSCT, compared 10 mg/kg rabbit-ATG. Therefore, we design this multicenter randomized study to evaluate the effect of 7.5 mg/kg and 10 mg/kg rabbit-ATG aiming at lowering viral infections without increasing GVHD in haplo-HSCT.

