### 9.1.3 Secondary Efficacy Endpoints

The incidence of grade II to IV and grade III to IV aGVHD within 100 days post-transplantation; hematopoietic engraftment; cGVHD; EBV-associated diseases; CMV infections (CMV DNAemia and associated diseases); relapse; non-relapse mortality (NRM); OS; DFS and tolerance.

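### The no-increase half of the stated aim on acute GVHD has no criterion in the current plan: the 15% margin is stated only for the initial design, and the analyses now given look only for a difference

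*Protocol*

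**What the plan says.** Section 9.1.1 of the protocol describes two designs. For the first it says "In the initial design, we predefined grade II to IV acute GVHD as the primary endpoint", with non-inferiority accepted if "the difference of the 95% CI in grade II to IV acute GVHD between the two groups was within 15" per cent. The size of that design was set as follows: "On the assumption of an incidence of grade II to IV acute GVHD of 30" per cent, "an estimated 197 patients in each group were required at the one-sided significance level of 5% with a power of 90" per cent.

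After an analysis of the first 210 patients the primary endpoint became EBV DNAemia. The stated purpose of the change was "to evaluate the superiority of a dose level of 7.5 mg ATG on viral infections without increasing aGVHD after haplo-HSCT". Section 1 expresses the same purpose: "aiming at lowering viral infections without increasing GVHD in haplo-HSCT".

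In the current plan:
- Section 9.1 states a superiority hypothesis for EBV DNAemia only, and the 412 patients are sized on that endpoint.
- Section 9.1.3 lists "The incidence of grade II to IV and grade III to IV aGVHD within 100 days post-transplantation" among the secondary endpoints, with no margin. Section 2.2 says only that aGVHD will be compared.
- Section 9.2.1 names the chi-square test, cumulative incidence curves with death as a competing risk, and Cox models.
- Section 9.2.2 adds "All P values are based on two-sided hypothesis tests", with alpha 0.05.

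**The concern.** The stated purpose has two halves: fewer viral infections, and no more GVHD. The first has a hypothesis, a sample size and a test. The second has none of these in the current text. A test of difference can reject equality. When it does not reject, it leaves open every increase inside the confidence interval, and here that interval can reach past the limit the sponsor itself once set.

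The question matters in this trial because the experimental arm receives less of the GVHD prophylaxis. Section 1 reports that in the group's previous single-centre study 6 mg/kg carried a higher risk of severe acute and of chronic GVHD than 10 mg/kg. More GVHD is therefore the foreseeable cost of the lower dose. A final report could show superiority on EBV and describe aGVHD as not increased, with no pre-stated basis for the second statement.

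**Working it through.** **Inputs.** From section 9.1.1: aGVHD 30%, margin 15 points, 197 per group for the initial design; EBV 30% vs 42%, one-tailed 5%, power 80%, 5% dropout, 206 per group for the current one. From section 9.2.2: two-sided alpha 0.05. Evaluable patients per arm: 206 × 0.95 = 195.7, taken as 196. Assumption: the 30% aGVHD rate of the initial design still describes the control arm. Simple proportions with normal approximations stand in for cumulative incidences.

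**1. The plan's own sample sizes.**
- Current: n = (1.645 + 0.842)² × (0.30×0.70 + 0.42×0.58) / 0.12² = 194.8, so 195; 195/0.95 = 205.3, so 206 per arm and 412 in total. This reproduces.
- Initial: n = (z_α + 1.282)² × 2×0.30×0.70 / 0.15². With z_α = 1.960 (one-sided 2.5%) n is 197. With z_α = 1.645 (the stated one-sided 5%) n is 160. The 197 therefore fits a two-sided 95% CI rule, which is the form used below.

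**2. Non-significant results that breach the margin** (196 per arm, control 30%). The test is z = d/√(2p̄(1−p̄)/n); the upper limit is d + 1.96√[(p₁(1−p₁) + p₂(1−p₂))/n].

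| Observed 7.5 vs 10.0 mg/kg | z | Upper 95% limit |
|---|---|---|
| 36% vs 30% | 0.06/0.0475 = 1.26 | 0.06 + 1.96×0.0474 = 15.3% |
| 39% vs 30% | 0.09/0.0480 = 1.87 | 0.09 + 1.96×0.0478 = 18.4% |

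Neither z reaches 1.96, and both limits exceed 15%. The upper limit passes 15% from an observed excess of about 5.8 points, and significance is reached only at about 9.5 points. At 206 per arm the corresponding values are about 6.0 and 9.2 points.

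**3. Power of a retained non-inferiority criterion** (30% in both arms, margin 15 points, one-sided 2.5%). Power = Φ(0.15/√(2×0.30×0.70/n) − 1.96).
- n = 196: Φ(3.240 − 1.960) = 0.900.
- n = 206: Φ(3.322 − 1.960) = 0.913.

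**4. The two approaches by true increase** (196 per arm, control 30%).

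| True rate, 7.5 mg/kg arm | Difference test detects | Difference test misses | Non-inferiority met |
|---|---|---|---|
| 38% | 0.386 | 61% | 31% |
| 40% | 0.546 | 45% | 18% |
| 45% (at the margin) | 0.869 | 13% | 2.5% |

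**The case against.** Several points on the other side are sound.

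- **Two inferences go beyond the text.** A reader might infer that the sponsor abandoned the non-inferiority test, or plans to read a non-significant P value as proof of no increase. The protocol says neither. It says that the primary endpoint changed, and it is silent on how the aGVHD half will be judged. The point rests on that silence next to a stated aim.
- **The SAP is not shown.** Section 9.2 refers to one, and it may keep the margin. The two-sided rule in section 9.2.2 would not forbid this, because a 95% CI criterion needs no P value. That stands. But the protocol presents the margin as belonging to a superseded design, so an SAP that kept it would go beyond what the protocol says.
- **The phrase is rationale, not a success criterion.** Section 2.1 makes EBV the only primary objective. This is correct, and it is why removing the phrase is an acceptable alternative.
- **The miss rates of 61% and 45% look alarming but are weak evidence.** They concern true increases of 8 and 10 points, inside the margin that the sponsor treated as acceptable. At the margin itself the difference test misses about 13%, against 2.5% false acceptance under the non-inferiority rule. The gain is real but smaller than the first two figures suggest.
- **The interim interval of -10.0% to 13.4% lies within 15%.** It gives partial reassurance on 210 patients. Nothing makes it the criterion for the final analysis of 412.

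**Conclusion.** The point holds as a mismatch between a retained aim and the analyses stated for it. As written, the current protocol gives no analysis that could support a claim of no increase in aGVHD. At 196 per arm and 30% in the control arm, observed excesses from about 6 to 9 points would be non-significant while the upper 95% limit lies above the protocol's own 15%. The result depends on the assumed 30% and on simple proportions; it changes little between 196 and 206 per arm.

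It should be fixed, but it does not invalidate the EBV comparison. A reader might go further and conclude that trial success must require both EBV superiority and aGVHD non-inferiority. The documents do not support that: EBV is the sole primary objective. The price would also be substantial. Assuming independence, joint power would be about 0.80 × 0.90 = 72%, or about 0.70 × 0.90 = 63% if EBV is tested two-sided.

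**What to change.** In sections 6.3 and 9.2.1, name 100-day grade II to IV aGVHD as a key secondary non-inferiority assessment, tested only after EBV superiority has been shown. It is met if the upper limit of the two-sided 95% CI for the difference in cumulative incidence (7.5 minus 10.0 mg/kg) is below 15%. State that a claim of no increase in aGVHD may be made only if this is met, and that a non-significant difference test does not support it. If the sponsor does not want this criterion, remove the no-increase wording from sections 1 and 9.1.1.

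EBV superiority stays the sole primary criterion. The margin covers grade II to IV aGVHD only, so meeting it would not support a no-increase claim for grade III to IV aGVHD or for chronic GVHD; the broader wording in section 1 should be narrowed to match.

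The cost is protocol text. No patients or data are added, and power is about 90% at 196 per arm if both arms are at 30%. The downside is that the no-increase statement may be unavailable even when EBV superiority is shown.
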